# The ACTonHEART study: rationale and design of a randomized controlled clinical trial comparing a brief intervention based on Acceptance and Commitment Therapy to usual secondary prevention care of coronary heart disease

**DOI:** 10.1186/1477-7525-12-22

**Published:** 2014-02-19

**Keywords:** Ischemic heart disease, Modifiable cardiovascular risk factors, Adherence, Psychological well-being, Quality of life, Acceptance and Commitment Therapy, Behavior modification, Randomized clinical trial

## Abstract

**Background:**

Modifiable risk factors, including life-style habits and psychological variables, have been increasingly demonstrated to have an important role in influencing morbidity and mortality in cardiovascular patients, and to account for approximately 90% of the population risk for cardiac events.

Acceptance and Commitment Therapy (ACT) has shown effectiveness in promoting healthy behaviors, and improving psychological well-being in patients with chronic physical conditions. Moreover, a first application of an acceptance-based program in cardiac patients has revealed high treatment satisfaction and initial evidences of effectiveness in increasing heart-healthy behaviour. However, no clinical trial to date has evaluated the efficacy of an acceptance-based program for the modification of cardiovascular risk factors and the improvement of psychological well-being, compared to usual secondary prevention care.

**Methods:**

Approximately 168 patients will be recruited from an outpatient cardiac rehabilitation unit and randomly assigned to receive usual care or usual care + a brief ACT-based intervention. The ACT group will be administered five group therapy sessions integrating educational topics on heart-healthy behaviours with acceptance and mindfulness skills. Participants will be assessed at baseline, six weeks later (post treatment for the ACT condition), at six and twelve months follow-up.

A partially-nested design will be used to balance effects due to clustering of participants into small therapy groups. Primary outcome measures will include biological indicators of cardiovascular risk and self-reported psychological well-being. Treatment effects will be tested via multilevel modeling after which the mediational role of psychological flexibility will be evaluated.

**Discussion:**

The ACTonHEART study is the first randomized clinical trial designed to evaluate the efficacy of a brief group-administered, ACT-based program to promote health behavior change and psychological well-being among cardiac patients. Results will address the effectiveness of a brief treatment created to simultaneously impact multiple cardiovascular risk factors. Conducted in the context of clinical practice, this trial will potentially offer empirical support to alternative interventions to improve quality of life and reduce mortality and morbidity rates among cardiac patients.

**Trial registration:**

clinicaltrials.gov/ (NCT01909102)

## Background

It has been demonstrated that modifiable risk factors play an important and influential role in the morbidity and mortality of cardiovascular patients [1-3] and account for more than 90% of the population risk for acute myocardial infarction (MI) [4]. A recent meta-analysis by Janssen and colleagues [5], which analyzed 23 randomized trials of primary and secondary care programs developed from 1999-2009, indicated that life-style modification programs may improve risk factors and related life-style behaviors, and reduce mortality, cardiac readmission, and non-fatal infarctions. However, research has shown poor long-term adherence to recommended behaviors among cardiac patients even after the application of life-style intervention programs [1,6-8]. Moreover, the majority of successful programs were both costly and labor intensive, utilizing numerous sessions and lengthy intervention periods [5,9-13]. These time- and cost-consuming interventions reduce the adoptability of the program to applied medical settings.

In the past, secondary prevention programs were almost exclusively focused on exercise. However, in order to address the multiplicity of cardiovascular risk factors, secondary prevention programs should provide integrated behavioral care including exercise, health education, lifestyle counseling, and psychological treatment to address a wide range of modifiable risk factors such as co-morbid presentations of both heart disease and depression for example [14].

As such, it is important that other interventions are developed and evaluated to address this shortcoming. ACT [15], a “third wave” behavioral and cognitive therapy, has a growing empirical base demonstrating its efficacy for a wide range of conditions [16,17]. ACT has been modified and empirically evaluated in several chronic physical illnesses with varying treatment lengths (3-hour workshop to 3-week retreats) [18]. ACT aims to maximize psychological flexibility, which is the ability to be fully present in each moment and to persist or change behavior in the service of personal values [16].

Applications of acceptance-based interventions have proven efficacious in fostering health behaviors, such as weight management [19,20], physical activity practice [21], and smoking cessation [22]. This model has been successfully adapted to improve adherence to medical prescriptions and adaptive functioning among patients with chronic physical conditions, such as diabetes [23], epilepsy [24,25], multiple sclerosis [26], chronic pain [27], and HIV disease [28]. All of these ACT-based interventions had short treatment durations, and were often administered in a group setting. A large scale, randomized trial investigating the effectiveness of an acceptance-based intervention to improve the health and quality of life among cardiac patients has yet to be conducted. However, a pilot study by Goodwin and colleagues [29] evaluated an application of an acceptance-based program for cardiac patients and provided initial evidence for effectively increasing heart-healthy behaviours. Moreover, participants in this study were highly satisfied with the intervention. In particular, results showed large improvements in diet and moderate increases in physical activity from pre- to post-treatment. However, given the absence of a control group and the small sample size of this initial investigation, large-scale randomized clinical trials (RCT) are needed to test the efficacy of ACT-based interventions with cardiac patients.

### Rationale for applying ACT to promote life-style changes and adherence among cardiac patients

ACT is mainly focused on improving psychological flexibility by fostering the ability to behave in a values-driven manner. Traditional cognitive behavior therapy attempts to dispute, change, and restructure the content of negative thoughts to reduce consequent psychological discomfort. Rather than modifying the content of thoughts, ACT attempts to change the relationship between the person and his own thoughts and feelings [30]. In the ACT model, experiential avoidance is defined as the attempt to alter the form, frequency, or situational sensitivity of difficult internal experiences such as thoughts, emotions, and physical sensations often resulting in increased distress [31]. Experiential avoidance may explain the difficulty patients experience when faced with behavior change despite knowledge of medical risks.

Adopting and maintaining a healthy life-style often entails distressing physical sensations, thoughts, and feelings; thus individuals with a low ability to tolerate distress might be less likely adopt and maintain behavioural changes. For example, changes in diet often require compromises in portion-size and taste [32-34], exercise is associated with physical discomfort and exercise-anxiety [21], and abstaining from nicotine is associated with cravings [22,35]. Moreover, lower medication adherence has been reported among HIV-positive patients avoiding distress [36]. Across domains, decreases in experiential avoidance may increase adherence to health-behaviours.

Another ACT process useful in explaining behavior change is the connection with key personal values, defined as long-term desired qualities of living [16]. When an individual loses contact with his life value, he may sacrifice long-term behavioral goals and values (e.g., adopting a healthy lifestyle) in the service of decreasing his very salient short-term goals (e.g., reducing present discomfort). Short- and long-term distress tolerance is necessary to adopt healthy (but strenuous) lifestyle changes.

Given ACT’s ability to address core theoretical processes proposed to contribute to behavior change, ACT appears to be particularly promising for increasing adherence to low-risk lifestyles among cardiac patients (e.g., low fat diet, smoking cessation, medication adherence)—a fundamental, but difficult goal to be attained.

### Rationale for promoting psychological well-being among cardiac patients using ACT

Given increasing evidence to suggest a causal association between mood, stress, and the development and prognosis of coronary heart disease [37-39], the management of psychological distress should represent an important goal of secondary prevention programs.

In the last decade many studies on psychological flexibility indicated an inverse association with a wide range of psychological outcome measures (e.g., depression, anxiety, job induced tension, worries, pain) and a positive association with quality of life, perceived health, and positive emotional experiences with medium effect-sizes [16,40-47]. Moreover, recent research on the ACT model suggests that psychological flexibility mediates the effects of adaptive coping strategies on emotional and psychological well-being [48,49].

Research to date supports the utility of ACT-based interventions to modify health-behaviours and reduce psychological distress. Thus, we propose that an ACT-based intervention maybe useful for improving the physical and psychological health of cardiac patients.

#### Study objectives and hypotheses

To the best of our knowledge this will be the first randomized controlled trial to evaluate the efficacy of ACT in cardiac patients. Thus, the main aim of this research is to examine the efficacy of a manualized ACT-group therapy program for preventing the long-term deterioration of several risk factors and lifestyle behaviors and for improving psychological well-being and quality of life in patients with IHD over a 12-months follow-up period. In order to reflect Medical Research Council recommended guidelines [50] as well as the multi-factorial nature of the intervention, a number of primary outcome measures will be considered.

Moreover, the study is aimed at exploring the mechanisms of change surrounding the intervention with increased psychological flexibility as a possible critical mediator of intervention effects.

Specifically, the current study is designed to test the following hypotheses:

Primary hypothesis: The proposed ACT intervention will be associated with significantly better achievement, compared to the usual care, in at least two of the following primary outcome measures: LDL-cholesterol, resting systolic blood pressure, body mass index, and psychological well-being measured by the Psychological General Well-Being (PGWB) Index.

As no RCT was available on ACT-based interventions for cardiac patients, at the time of the study design we were not able to predict the modification of these four outcome variables as effect of the intervention.

Otherwise, expected levels of change on some of these indicators can be projected for participants in the usual care condition based on the GOSPEL study [51], a recent Italian survey on a similar population. Results from this study showed time-related worsening of the management of cardiac risk factors at 12-months follow-up. In particular, in the usual care condition, the following mean changes from baseline to 12-months follow-up were observed: an increase of 0.4 mg/dl in LDL cholesterol levels, an increase of 0.4 Kg/m^2^ in BMI and a 15.2% decrease in the rate of patients at target for resting systolic blood pressure [51].

We hypothesize that participants in the usual care group will show mean changes in the aforementioned variables comparable to those founded in the GOSPEL study, while patients in ACT condition will achieve better results on these primary outcomes with a medium between-group effect size (a standardized mean difference between mean changes of at least 0.3 standard deviations is expected).

*Secondary hypotheses:* The intervention will also improve a number of secondary outcomes: *1.* adherence to a heart-healthy lifestyle (increased physical activity; improved dietary patterns, smoking status, medication adherence); 2. perceived health-related quality of life; 3. other biological indicators of cardiovascular risk (exercise capability during an incremental bicycle stress test, lipid profile, glycosylated haemoglobin level, and waist to hip ratio).

*Mediation hypotheses:* The intervention will improve levels of psychological flexibility and the change in this variable will be associated with change in outcome variables.

## Methods

### Study design

This is a prospective randomized controlled clinical trial. It is a two-arm, partially nested design with three follow-up assessments (at the end of the treatment period, 6 and 12 months). Participants in the ACTonHEART condition will be provided usual care plus an ACT-based group program while those in the control condition will receive standard usual medical care. Indeed, according to the Medical Research Council guidelines [50] the ‘usual treatment’ may be more appropriate than a placebo condition in the case of trials evaluating complex interventions.

The study protocol was approved by The Istituto Auxologico Ethics Committee (2007000303).

#### Usual general practice care

Participants in both conditions will receive a standardized outpatient CR program designed in accordance to the best EU practice [14]. The program is individually tailored and conducted by a multi-disciplinary team. The CR physician is responsible for prescribing medication according to guidelines. The program has an average duration of 6-weeks and includes exercise training, psycho-education, and behavioral counselling by the CR team or a private practitioner. A letter will be sent to family physicians recommending secondary prevention goals. After the standard care period, patients will be asked to report to the hospital to complete a 6-month and 12-month assessment consisting of laboratory and exercise tests. After each assessment, a copy of said results will be forwarded to the participant’s family physician, who will continue to provide on-going treatment and medical advice as needed. In addition to standard care, the ACTonHEART group will receive the ACT intervention.

#### The ACTonHEART intervention

Participants randomly assigned to the ACTonHEART condition will complete five 90-minutes sessions over the course of 6-weeks based on ACT with the aim of positively modifying health-related behaviors and improving psychological health. The program will be developed on the basis of ACT-consistent protocols adapted from a) Goodwin and colleagues’ Acceptance Based Behavior Therapy (ABBT) for cardiac patients [29] and b) Acceptance-based treatment for the self-management of diabetes [23]. The program integrates educational topics on heart healthy behaviours with mindfulness and acceptance training, address difficult thoughts and feelings, clarification of health-related values, and behavioral commitment. The intervention will be administered by two interventionists (ACT therapist and doctoral-level student) in treatment groups of 8 participants.

Sessions 1-4 of the intervention will be delivered weekly, followed by a two week break between session 4 and 5. The content of each group-session will be structurally flexible, and include both didactic and experiential and metaphorical examples.

The sessions will be conducted at the cardiac rehabilitation gymnasium and each of them will last 90 minutes.

The ACTonHEART intervention will include the following four components:

*Cardiac education,* which consists of providing information about recommended diet, exercise, and the effects of risky behaviors such as smoking and poor adherence to medication. Additionally, specific behavioral techniques will be presented to address some of the common barriers to adoption of a heart-healthy lifestyle. Moreover, each session will include group problem-solving to address barriers to meeting individual behavioral goals.

*Mindfulness*, refers to engaging in one’s present moment experience and adopting an open and curious attitude instead of struggling with moment, even if the moment is unpleasant [15,52]. Additionally, mindfulness aims to increase self-awareness by noticing all internal experiences (positive and negative) in the moment. Previous control-based attempts to cope with cardiovascular disease, such as avoidance of disease cues, unpleasant thoughts and sensations, will be explored to demonstrate the ineffectiveness of control when pursuing a meaningful life. Participants will be encouraged to defuse from thoughts and feelings by turning attention toward the ‘noticing-self’ (termed defusion) instead of becoming attached to thoughts and maneuvering through life on ‘auto-pilot’.

*Acceptance and willingness*, involves the active awareness and embrace of difficult private internal experiences without unnecessary attempts to control or avoid unpleasant emotions. Acceptance is an alternative to experiential avoidance. Participants will be taught to increase adherence to a heart-healthy lifestyle by increasing willingness to experience distressing sensations and urges moment to moment (i.e., acceptance) while engaging in health behaviors. By encouraging participants to live in accordance with their values, participants can engage in meaningful/pleasurable activities despite experiencing unwanted emotions/sensations.

*Values, goals and committed action*. Identification of participant values and related behavioural goals will increase engagement in values-driven behavior, or committed action. Potential barriers to adopting value-driven behaviours and maintaining committed action in the long-term will be explored and addressed through metaphors and experiential techniques.

### Participants, setting, and assignment

All participants referred to the outpatient CR unit at S. Luca Hospital, Istituto Auxologico Italiano, Italy, will be invited to participate in the study. Patients who wish to participate will be screened for inclusion and exclusion criteria.

Patients who will meet the following inclusion criteria will be eligible for the study:

a) A definite diagnosis of IHD including recent (< 8 weeks) acute MI, acute coronary syndrome, surgical revascularization (Coronary Artery By-pass Surgery)

b) Major modifiable cardiovascular risk factors assessed using the INTERHEART Modifiable Risk Score [53]; higher scores indicate greater risk. Only subjects with a full score > 9 will be included in the study

c) Age between 18 and 70 years

d) Fluency in spoken and written Italian language

e) Expression of written informed consent

Exclusion criteria for the study are: a) severe psychiatric disorders according to DSM-IV TR criteria [54] b) mental incapacity to participate in the programme (e.g. cognitive impairment).

### Assessment procedure

Participants will be asked to complete all study measures before randomization. Follow-up repeated measures assessment will be completed on all study participants six weeks later (post treatment), and at 6- and 12-month follow-up.

Demographic data such as gender, age, marital status, level of education, and employment status will be assessed in order to control for these potential confounders.

Medical data such as recurrence of cardiac events and additional diagnoses (e.g. diabetes) that may confound results will be retrieved from clinical records. Furthermore, a listing of participants’ current medications and dosages at each time point will be used to assess the degree to which the intervention is affecting change above and beyond medication effects.

Participants in both groups will provide a history of any psychological treatment or counselling to assess potential familiarity with mindfulness- and acceptance-based therapies.

A range of physiological and psychological outcome measures will assess the following: modifiable cardiovascular risk factors, adherence to medication and recommended life-style, and psychological well-being and quality of life.

Adjusted change scores for all the outcome measures will be calculated in order to assess the interventions ability to produce changes over time.

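### The planned effect beyond medication conditions on drug use recorded after randomisation, so randomisation does not protect that estimate

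*Protocol article*

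**What the plan says.** All of the following is in the protocol article.

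- *Assessment procedure* says of the patients' listed drugs that "dosages at each time point will be used to assess the degree to which the intervention is affecting change above and beyond medication effects". The sentence just before it concerns "Medical data such as recurrence of cardiac events and additional diagnoses (e.g. diabetes) that may confound results".
- The same section fixes the timing. Baseline measures precede randomisation, and "Follow-up repeated measures assessment will be completed on all study participants six weeks later (post treatment), and at 6- and 12-month follow-up".
- It then states that "Adjusted change scores for all the outcome measures will be calculated", without naming the adjustment variables.
- *Study objectives and hypotheses* lists, among the secondary effects expected of the intervention, "improved dietary patterns, smoking status, medication adherence". *The ACTonHEART intervention* says that the sessions inform patients about "the effects of risky behaviors such as smoking and poor adherence to medication".
- *Usual general practice care* covers both arms: "The CR physician is responsible for prescribing medication according to guidelines". After the 6- and 12-month assessments, which consist of laboratory and exercise tests, "a copy of said results will be forwarded to the" family physician, who carries on treating the patient.
- *Statistical analysis* tests the four primary outcomes in a partially nested multilevel model. Its named covariates are exploratory moderators, and psychological inflexibility is its only named mediator. Medication does not appear there as a covariate or a mediator.

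**The concern.** Randomisation balances what exists at baseline. A drug list at six weeks, 6 months or 12 months, or a recurrent event during follow-up, comes later. It may be a consequence of the assigned arm, of earlier outcome values, or of unmeasured severity and health behaviour that also drive the outcome. Treating it like a confounder can remove part of the real effect and can also create an association between arm and those unmeasured causes.

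The conclusion at stake is the one the sentence sets up: that ACT changes risk factors by some amount over and above drugs. LDL-cholesterol and systolic blood pressure can both respond to drugs. They are two of the four primary outcomes, and the primary hypothesis asks for benefit on at least two. A beyond-medication figure for either would be read as explaining the main result, although randomisation does not support it.

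**Working it through.** The plan gives no figure on this point, so there is none to reproduce. The check sets the statements side by side and then illustrates the mechanism.

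**Timing and routes**

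1. Of the four medication lists, only the baseline list precedes randomisation. Recurrent events follow it. The additional diagnoses are undated and may be baseline comorbidity.
2. Arm to medication: adherence is both session content and a secondary target. The list records drugs and doses, which physicians set. A shift in prescribing by arm is therefore plausible but not stated.
3. Outcome to medication: the 6-month laboratory results reach the physician who continues treatment, so the 12-month list can respond to 6-month LDL. The 12-month results are sent too late to alter the 12-month list, and no forwarding is described for the six-week assessment. Resting blood pressure is not named among the forwarded results, so this route is firmest for LDL.
4. By routes 2 and 3, 6-month LDL can be affected by the arm and can influence both 12-month medication and 12-month LDL. It is then a treatment-affected confounder, and ordinary covariate adjustment does not recover a direct effect in its presence.

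**Illustration**

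Let T be the arm, M follow-up medication, Y the outcome (benefit positive) and U an unmeasured severity or health behaviour:

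- M = a·T + k·U + error, with variance 1 within arm
- Y = direct·T + 0.3·M + u·U + error
- Total effect = direct + 0.3·a, fixed at 0.30, the protocol's standardised effect

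Within arm, the expected U given M is k·(M − a·T). The coefficient of T in a model that includes M is therefore direct − a·k·u. The values of a, k, u and the 0.3 medication effect are assumptions. The outcome variance within arm is 1 + 2·0.3·k·u, that is 0.85 to 1.15, so the units are close to one SD. Each scenario was also simulated with 400,000 patients.

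| a | k | u | True direct effect | Adjusted for M (formula) | Adjusted for M (simulated) |
|---|---|---|---|---|---|
| 0 | 0 | 0 | 0.30 | 0.30 | 0.298 |
| 0 | 0.5 | 0.5 | 0.30 | 0.30 | 0.292 |
| 0.2 | 0 | 0 | 0.24 | 0.24 | 0.243 |
| 0.4 | 0 | 0 | 0.18 | 0.18 | 0.180 |
| 0.4 | 0.5 | 0.5 | 0.18 | 0.08 | 0.078 |
| 0.4 | 0.5 | −0.5 | 0.18 | 0.28 | 0.279 |
| −0.2 | 0 | 0 | 0.36 | 0.36 | 0.362 |
| −0.2 | 0.5 | 0.5 | 0.36 | 0.41 | 0.411 |

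For example, in the fifth row: 0.30 − 0.3×0.4 = 0.18, then 0.18 − 0.4×0.5×0.5 = 0.08. Without M in the model, the simulated estimate stayed between 0.296 and 0.304 throughout.

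Three things follow. With a = 0, adjustment does no harm. With a ≠ 0 and no U, the adjusted figure equals the direct effect but not the total effect. With a ≠ 0 and U present, it is neither, and the error can go either way.

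**The case against.** The strongest reply is that the article specifies no such adjustment. The sentence names no model and no outcome. It could mean describing medication by arm, or a supplementary direct-effect analysis, and either would be acceptable if labelled. The Statistical analysis section leaves medication out of the primary model, out of the named moderators and out of the mediation analysis. The drugs are prescribed by physicians following guidelines in both arms, whereas the intervention targets adherence, which has its own scale. If the arms do not differ in medication there is no bias. Baseline medication, which the sentence also covers, is a legitimate covariate.

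Much of this stands. A reader might infer that the primary treatment comparison is biased, or that the primary tests lose power. The documents do not support either inference: no primary model with follow-up medication is stated, the beyond-medication analysis is nowhere called confirmatory, and no share of the effect running through drugs is given.

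It does not remove the point. The sentence states a purpose, an effect separated from medication, and includes follow-up data in it. The sentence before it calls recurrent events possible confounders, which they cannot be for a randomised comparison. Intention-to-treat, which the article promises, decides who is analysed in which arm; it does not exclude covariates measured after baseline. The adjusted change scores, undefined in the same section, leave open whether these variables reach the main comparison.

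**Conclusion.** The point holds for the beyond-medication estimate. As worded, the plan would use post-randomisation variables to isolate part of the treatment effect without stating the two assumptions that this needs: no unmeasured medication–outcome confounding, and no such confounding affected by treatment. The second is doubtful for LDL because of the 6-month report to the family physician.

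The size cannot be derived from the documents. The illustrated range, 0.08 to 0.41 against a total effect of 0.30, shows only that the direction is not fixed; it depends on the arms differing in medication and on the assumed inputs. For the primary comparison the point is conditional: it applies only if the adjusted change scores take in follow-up medication or recurrent events. This is worth correcting before analysis, but it is not a demonstrated bias in the main result.

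**What to change.** - State that treatment effects on all outcomes are estimated regardless of medication changes and recurrent cardiac events.
- Define the adjusted change scores, with adjustment only for baseline values, which may include baseline medication and baseline diagnoses.
- Stop describing recurrent events as confounders. Report them, and medication change, by arm.
- Label any beyond-medication analysis as an exploratory mediation or direct-effect analysis. State its confounding assumptions and how variables affected by treatment, such as 6-month LDL, are handled.

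The cost is wording only. The same data are collected and patient care does not change. The one loss is that a claim of benefit beyond medication becomes exploratory.
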